#### Interim analyses {21b}

N/A. This study does not include an interim analysis.

#### Methods for additional analyses (e.g., subgroup analyses) {20b}

N/A. This study does not include a pre-defined list of participant demographic characteristics for purposes of subgroup analysis.

#### Methods in analysis to handle protocol non-adherence and any statistical methods to handle missing data {20c}

Participants with < 70% of scheduled ABPM measures or incomplete data capture (< 70%) with other measures of interest will be classified as “incomplete.” These data will be analyzed separately from participants with complete data.

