### Trial design {8}

We will use a randomized crossover trial study design with three study arms/conditions. All three conditions will involve continuous monitoring over 72 h and will begin with a 36-h at-home period, followed by 24 total hours in the lab (including a 12-h simulated night shift), and ending with 12 h at home. The key difference between the three conditions is the presence or absence of an intra-shift nap and the duration of that nap. Condition 1 will involve a simulated 12-h night shift with no nap: total sleep deprivation. Condition 2 will comprise another simulated 12-h night shift and a 30-min nap opportunity. Condition 3 will involve a simulated 12-h night shift and a 2-h nap opportunity. There will be a mandatory 1–3 week washout period between conditions. The order in which participants complete the study conditions will be balanced by a William’s square design. In the paragraphs below, we outline the details of our experimental study in accordance with the CONSORT/SPIRIT statement. Figure 1 illustrates the flow chart of our trial, and Fig. 2 illustrates the SPIRIT template for enrolment, intervention, and assessment. The University of Pittsburgh Institutional Review Board (IRB) approved this study {24}, and our protocol has been registered with ClinicalTrials.gov ({2a} registration number: NCT04469803; public release date: 9 July 2020). All subjects are required to provide written informed consent (see Additional file 1, which reports on all elements of the SPIRIT checklist). All elements of the World Health Organization Trial Registration Data Set can be found in this article, supplemental file, and the ClinicalTrials.gov registration.

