### Intervention description {11a}

Our intervention of interest is intra-shift napping. All subjects in our study protocol will participate in two intervention nap conditions and one no-nap comparison condition. All nap opportunities will be available between 0200 and 0400 h during the in-laboratory phase and simulated night shift. We chose this time period given that (A) EMS call volume (workload) is often low or limited at this time, and many who are allowed to nap on duty may use this time period for sleep, and (B) this window of time coincides with a known time of high homeostatic sleep pressure and minimal circadian alerting signal [21]. Protocol conditions 2 and 3 will involve scheduled intra-shift nap opportunities of 30 min and 2 h, respectively. Our choice of 30 min and 2 h for the nap opportunities was based on the following: (A) previous research has suggested that short duration naps are optimal during night shift work for sustained or improved performance and avoidance of sleep inertia (that groggy feeling experienced upon waking) [8]; (B) shorter duration naps are attractive in public safety because EMS work is unpredictable and when called upon, an EMS worker must react quickly and make medical decisions to care for the acutely ill and injured; (C) many EMS employers who may not endorse sleeping while on duty might be amenable to short versus longer opportunities for intra-shift napping [51]; and (D) blood pressure and HRV are tightly tied to sleep and depth of sleep [9]. As described previously, normal dips in BP and parasympathetic-driven changes in HRV often occur when entering deeper, slow-wave sleep, which can occur 30 min or longer after beginning sleep [9, 53]. Therefore, the longer 2-h nap condition may be superior in terms of a cardiovascular-focused health benefit than would the shorter 30-min nap condition.

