### Criteria for discontinuing or modifying allocated interventions {11b}

Participation is voluntary; thus, participants may withdraw at any time for any reason, which may include self-reported inability to complete the study protocol as designed. Criteria for orderly discontinuing a participant’s involvement in the study include the following: (A) the participant voluntarily withdraws from the study, (B) the participant does not complete all procedures/visits per protocol, (C) the participant’s physician or one of the investigators feels that it is not in the best interest of the subject to be in the study (i.e., severe hypertension or hypotension), and (D) the participant’s BP exceeds a measurement value of 180/110 across multiple measures. In the event that a participant’s BP averages exceed the value of 180/110 while being measured in the presence of the study team, the study team will direct the participant to contact his/her healthcare provider to discuss the measures. There are no pre-defined criteria for modifying allocated interventions.

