### Outcomes {12}

Our primary outcomes of interest include blunted BP dipping and reduced HRV as measured by the standard deviation of the inter-beat intervals of normal sinus beats (SDNN). Blunted BP dipping will be calculated using two measures. First, we will quantify sleep vs. wake BP dipping by identifying the participant’s sleep and wake times and stratifying the hourly ABPM measures into sleep vs. wake measures. The ratio of sleep-to-wake BP is calculated by taking the difference between the mean systolic and diastolic BP during the sleeping hours and the mean systolic and diastolic BP during waking hours. We define dipping status as follows: (mean wake hours BP − mean sleep BP divided by mean wake hours BP) × 100. Non-dipping status will be defined as sleep hours BP dip of less than 10%, assessed with systolic BP (SBP) and diastolic BP (DBP) [22, 69]. Next, we will stratify each 24-h period into nighttime vs. daytime periods and calculate nighttime BP dipping with the “wide fixed time method” [70, 71]. Daytime hours are defined as 0700 to 2259 h, and nighttime hours are defined as 2300 to 0659 h [70, 71]. The ratio of night-to-day BP is determined by taking the difference between the mean systolic and diastolic BP during the nighttime hours (2300 to 0659 h) and the mean systolic and diastolic BP during daylight hours (0700 to 2259 h). For this method, nighttime dipping status is determined as follows: ((mean daylight BP − mean nighttime BP) ÷ mean daylight hours BP) × 100. We will assess dipping vs. non-dipping status during sleep hours and during nighttime hours for all periods of observation and for all study conditions.

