### Data collection and management

#### Plans for assessment and collection of outcomes {18a}

The protocol for measurement assessment and collection of outcome measures includes the use of continuous monitoring devices, such as ABPM for serial BP measurement, and cardiac Holter monitoring for serial HRV measurement for the 72-h protocol repeated three times for each study participant. For ABPM, we will assess BP hourly with the Oscar2 device manufactured by SunTech Medical (Morrisville, NC, USA). For HRV, we will use the NASIFF CardioCard® 5-lead, 3-channel device (NASIFF Associates, Inc., Central Square, NY, USA). As described in the “Outcomes {12}” section, we will administer surveys at baseline and again at pre-specified time points in order to capture subjective ratings of sleep and fatigue. Our plan for assessment will also include monitoring of sleep depth during the conditions that involve intra-shift napping. We will use the Zmachine® Synergy for purposes of assessing depth of sleep during the in-laboratory phase only and only during the two napping conditions. Sleep versus wake will be assessed with a wrist-worn actigraphy device (wGT3X-BT by Actigraph Corp., Pensacolo, FL, USA) worn continuously during the three 72-h protocols.

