### Statistical methods

#### Statistical methods for primary and secondary outcomes {20a}

We will report the demographic characteristics of the study sample using descriptive statistics and stratify the final dataset into two categories for the main analysis. These categories will be labeled as “complete” and “incomplete data.” We will further describe the average systolic and diastolic BP, the incidence of blunted BP dipping, and the proportion of participants with blunted BP dipping. Blunted nocturnal BP dipping will be defined as previously described. Our second outcome of interest is HRV. As prescribed [72], we will examine HRV based on five time-based measures summarized over each 24-h period of observation.

To address the impact of napping on BP dipping, we will conduct paired *t* tests to determine if the mean amount of BP dipping differs across conditions. Generalized linear mixed models (GLMM) with participant-specific random effects will be utilized to compare the odds of blunted BP dipping across conditions. We will evaluate the distribution of residuals at each level of the models for linearity and heterogeneity. We will check for outliers and influential observations and sets of observations. The distribution of the data will be examined, and transformations will be performed as necessary for valid comparisons. We will use GLMM to estimate and compare the proportion of EMS workers with blunted BP dipping and control for the dependence between repeated measures within each participant with a random subject effect.

To address the impact of napping on select measures of HRV, we will use GLMM with appropriate distribution and link function to estimate and compare HRV measures between EMS workers across the three conditions. We will again account for the within-participant correlation of repeated measurements and any participant-dependent covariates that vary in the study sample. The least square means and corresponding 95% confidence intervals will be calculated from the models for each group and the difference between groups.

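### The main analysis separates whole participants by a 70% any-device capture rule, which keeps usable within-person contrasts out of the complete-data estimate and does not secure the readings that define the BP dip

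*Protocol article*

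**What the plan says.** Section {20c} sets the rule at the level of the person: "Participants with < 70% of scheduled ABPM measures or incomplete data capture (< 70%) with other measures of interest will be classified as" incomplete. It continues: "These data will be analyzed separately from participants with complete data". Section {20a} makes this part of the primary work, since the authors will "stratify the final dataset into two categories for the main analysis", one labelled complete and the other incomplete.

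The measurement schedule is in other sections. On frequency, {18a} says: "For ABPM, we will assess BP hourly with the Oscar2 device". On duration, {8} says: "All three conditions will involve continuous monitoring over 72 h". For the fixed-time dip in {12}, "nighttime hours are defined as 2300 to 0659 h"; the other dip measure compares sleep with wake. The intervention section {11a} describes "scheduled intra-shift nap opportunities of 30 min and 2 h, respectively".

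Section {20a} plans paired t tests for mean dip, and generalized linear mixed models with participant random effects for the odds of blunted dipping and for HRV. Section {14} expects 10 of 35 enrolled not to complete. Section {11b} lists among its discontinuation criteria that "the participant does not complete all procedures/visits per protocol".

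**The concern.** The rule is fixed at the wrong level in two respects.

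First, it classifies people, not outcomes or periods, and shortfall on any one measure is enough. A crossover participant with a partial record can still supply a valid within-person comparison, but under this rule that comparison does not enter the complete-data estimate.

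Second, a percentage of all scheduled readings says little about whether the few readings behind the night or sleep mean were obtained. A participant can pass the threshold without a computable fixed-time dip for the simulated night shift.

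At stake are precision in a small trial and the population the estimate describes. Membership of the complete group is decided by data capture after randomisation, so the estimate depends on who kept the devices working and finished all three conditions. The planned mixed models can use partial records under a missing-at-random assumption, and the split gives that up. With about 10 participants expected not to complete, a separate analysis of the incomplete group is unlikely to be informative.

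**Working it through.** **1. The plan's own power figure.** Inputs from {20a}: n = 25, difference 5 mmHg, within-participant SD 6 mmHg, two-sided alpha 0.05.
- SD of a paired difference: 6 × √2 = 8.49.
- Standard error: 8.49/√25 = 1.697. Noncentrality: 5/1.697 = 2.946, with 24 df.
- Paired t power: 80.7%. The smallest n reaching 80% is 25.

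The stated 80% therefore reproduces, with almost no slack.

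**2. Reading counts.** Hourly readings over 72 h give 72 per condition and 3 × 72 = 216 in all. The 2300–0659 window holds 8. A 2-h nap holds about 2, and a 30-min nap holds 0 or 1. Section {20c} does not state the denominator of the 70%, so three are shown.

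| Denominator | Readings needed | May be lost | All 8 shift-night readings of one condition lost | Both 2-h nap readings lost |
|---|---|---|---|---|
| 24 h | 17 (0.7 × 24 = 16.8) | 7 | 16/24 = 66.7%, incomplete | 22/24 = 91.7%, complete |
| 72 h | 51 (0.7 × 72 = 50.4) | 21 | 64/72 = 88.9%, complete | 70/72 = 97.2%, complete |
| 216 | 152 (0.7 × 216 = 151.2) | 64 | 208/216 = 96.3%, complete | 214/216 = 99.1%, complete |

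Over 216 readings, even losing all three simulated-shift nights (24 readings) leaves 192/216 = 88.9%, complete.

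**3. Usable data set apart.**
- Full ABPM with Holter capture under 70%: incomplete under the wording of {20c}, for BP as well. This needs no assumption about the denominator.
- Two full conditions and none of the third: 144/216 = 66.7%, incomplete if the count runs over all 216 readings, although one full within-person contrast was observed.

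**4. What the split costs.** The documents do not say how many conditions the 10 non-completers will finish, so the patterns below are assumed. The model is a linear mixed model with within-participant SD 6 and an assumed between-participant SD of 6. Partial records are spread evenly over conditions. The standard error of a pairwise contrast c is √(c′(ΣX′V⁻¹X)⁻¹c), with V = 36·I + 36·J for each participant's observed conditions (I the identity, J a matrix of ones). Power is from the noncentral t with noncentrality 5/SE.

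| Data used | SE | Power |
|---|---|---|
| 25 completers only | 1.697 | 82.3% |
| 25 with three conditions, 5 with two, 5 with one | 1.586 | 87.2% |
| 25 with three conditions, 10 with one | 1.643 | 84.7% |

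The completers' 82.3% exceeds the 80.7% in step 1 because the three-condition model has more residual degrees of freedom (48 against 24). Moving the between-participant SD from 3 to 10 changes the 87.2% only to between 88.0% and 86.5%.

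**5. If low capture also reduces the 25.** Section {14} allows for non-completion and attrition and does not mention low capture. If 4 of the 25 were classed incomplete, n = 21: SE = 8.49/√21 = 1.852, noncentrality 5/1.852 = 2.700, paired t power 72.9%.

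**The case against.** Several stronger readings are tempting, and the documents do not support them.

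- **The incomplete data are thrown away.** They are not: they are analysed separately, and both categories are named for the main analysis. What stands is that they add nothing to the complete-data estimate.
- **A whole lost night always passes.** This depends on the unstated denominator. Section {12} works in 24-h periods, and a per-24-h count would catch it. The 67% example likewise needs the 216-reading count. The nap readings go unprotected under all three counts, but their scarcity comes from hourly sampling, and no completeness threshold would cure that.
- **The estimate is biased.** Completers in a crossover still give randomised within-person contrasts. Bias requires missingness related to condition-specific outcomes, and nothing in the document shows that. Section {14} also plans to compare those who stop with those who finish. That comparison can reveal differences but does not bring partial records into the estimate.
- **The trial is underpowered.** It is sized to leave 25 after 10 losses, and 25 suffices. On the expected loss the split forgoes extra power and creates no shortfall. The 73% needs four further exclusions that the document does not predict.
- **The discontinuation criterion removes completed conditions.** Section {11b} does not mention the 70% rule or say what happens to data already collected.

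The missing denominator alone could fairly be left to a fuller document. The person-level, any-device split in the main analysis could not, because the article states it outright.

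**Conclusion.** The concern holds as a fault in how the main analysis set is defined. As written, one failed device can take a participant's sound data on another outcome out of the complete-data estimate, and passing the threshold does not ensure that the night or nap readings exist.

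The measurable cost is moderate. It is about 5 points of power under the assumed 25/5/5 pattern (82.3% against 87.2%), and about 2 points if all ten non-completers finish one condition only (84.7%). These figures rest on the assumed completion patterns and the assumed between-participant SD, so they are illustrative. The fall to 73% is conditional on 4 of the 25 being classed incomplete. Dependence on post-randomisation capture follows from the text; selection bias from it is a possibility only.

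**What to change.** In {20a} and {20c}:

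1. Make the main analysis one mixed model per outcome, including every randomised participant with valid data for that outcome in at least one condition. For mean dip this replaces the paired t tests with a linear mixed model.
2. State that the completed conditions of participants who discontinue stay in the analysis.
3. Judge validity per outcome and per analysis window (day or wake, night or sleep) by a minimum number of valid readings, in place of one percentage per person across devices.
4. Keep the 70% complete-only set as a sensitivity analysis.

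The cost is revised wording, a little more analysis work and reliance on a missing-at-random assumption, which the complete-only sensitivity analysis helps to probe. No additional data are needed. The change should be made before the data are analysed, so that the choice of dataset cannot be seen as driven by results.

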#### Plans to give access to the full protocol, participant-level data, and statistical code {31c}

Study-related materials and study-related data would be made available upon request and with permission and approval from the University of Pittsburgh. All requests must be reasonable.

### Oversight and monitoring

#### Composition of the coordinating center and trial steering committee {5d}

This study does not include a coordinating center. The study principal investigator and two co-investigators will be responsible for monitoring and managing data quality, assess completeness and accuracy of data collection, implementation and adherence to the study protocol, and measurement of outcomes.

#### Composition of the data monitoring committee, its role, and reporting structure {21a}

Study-related progress and data (e.g., enrolment, withdrawals) will be reported monthly to the University of Pittsburgh, Department of Emergency Medicine Departmental Clinical Research Meeting (DCRM). The DCRM comprised the department’s vice chair of research, senior faculty, study coordinators, and department liaisons with the university’s institutional review board. The members receive monthly updates, provide feedback to investigators, and advise on study-related challenges and events that may have been or need to be reported to the university’s institutional review board and/or funding organization.

#### Frequency and plans for auditing trial conduct {23}

All data maintained electronically in the REDCap database will be examined for accuracy (quality) and reported during the monthly DCRM meetings.

#### Plans for communicating important protocol amendments to relevant parties (e.g., trial participants, ethical committees) {25}

All protocol modifications or amendments will be reported (submitted) to the University of Pittsburgh Institutional Review Board. Participants will be notified of the amendments or modifications that impact participation, confidentiality, or safety.

#### Dissemination plans {31a}

Our plan for dissemination includes peer-reviewed manuscripts and presentations at professional meetings.

## Discussion

Paramedics and EMTs are essential front-line public safety workers who face excess risk of workplace injury, mental stress, fatigue, poor sleep quality, and poor health and well-being. The workforce is limited and poorly compensated, which is evidenced by a large proportion working multiple jobs or excessive hours of overtime. There is great uncertainty regarding the optimal duration of an intra-shift nap, how best to implement a napping program, and how napping may impact performance and worker health. Our study will address worker health outcomes, specifically two indicators of cardiovascular health, and determine if shorter or longer duration naps during night shifts have a clinically meaningful impact. Our study will also assess recovery of these indicators immediately post-night shift, which will provide additional information for decision-makers and individual EMS workers.

The experimental protocol outlined in this paper is novel for the following reasons: (A) it builds on recent evidence-based guidelines that promote intra-shift napping for fatigue mitigation, (B) the study will involve EMS clinicians as study subjects and therefore provide much needed direct evidence as opposed to indirect evidence involving “non-EMS” volunteers, and (C) our outcomes of interest include key indicators of cardiovascular disease. With few having assessed these outcomes in this population [99], under these conditions, the results of this study will provide new insights for researchers and additional evidence to guide decision-making.

One key component of our study is the comparison of the shorter (30 min) nap to the longer (2 h) nap. There are relatively few studies comparing shorter and longer duration naps [57, 62], and even less information about nap duration germane to EMS work [50]. Many in public safety would likely favor shorter duration naps given the potential for sleep inertia and how it can negatively impact performance immediately upon waking [8, 51]. The favorability of longer-duration naps is unknown. However, data from our recent observational study of 56 EMS night shift workers shows that longer duration naps (e.g., > 60 min) offer greater benefits to cardiovascular health than shorter naps in the form of a healthy dip in BP [35]. The study protocol outlined in this paper will help clarify the differences and similarities of different nap durations for EMS workers. It is plausible that we discover shorter duration naps are nearly as beneficial as longer duration naps for key indicators of cardiovascular health. It is also equally plausible that we discover longer duration naps are needed in order to observe benefit in the form of a healthy dip in BP. Regardless of our findings, the results will be informative to local EMS employers and decision-makers responsible for fatigue mitigation and workplace wellness.

